### Additional consent provisions for collection and use of participant data and biological specimens {26b}

N/A. No other consents are needed from participants since the data collected will be used for the sole purpose of the study and no biological specimens will be collected.

## Interventions

### Explanation for the choice of comparators {6b}

Participants will be randomized to the active taVNS or sham taVNS. To reach an effective stimulation of the vagus nerve through taVNS in the active condition, the electrodes will be placed at the left ear concha. The ear concha is principally innerved by the afferent branch of the vagus nerve (ABVN) [52]. In the sham taVNS condition, the stimulation electrodes will be placed at the center of the left ear lobe, which is known to be free of cutaneous vagal innervation [65] and the electrical stimulation at this anatomical area is not able to activate the vagus pathway [66] (Fig. 1). This method was chosen because it has the advantages that it has already been used in several sham-controlled studies [60, 67–69], it is easy to use, and the participants can still feel a tickling sensation as for the active taVNS, making it more difficult to distinguish between the active and the sham conditions. The disadvantages are that the participants may have seen pictures of the active taVNS electrode placing leading to a possible unblinding and that the innervation of the ear lobe is still not completely clear leading to possible unwanted effects.

**Fig. 1 Fig1:**
[figure not shown]
Positioning of the stimulation electrodes in the active (left) and in the sham (right) condition

### Intervention description {11a}

The participants will sit comfortably in front of a computer monitor, with an adjustable height chair, and will be reminded of the potential provocative nature of the task (i.e., that the clips will contain profane language, sexual content, and violence). Three electrocardiographic (ECG) electrodes will be applied at the right collar and at the right and left lowest rib cage bones and two galvanic skin response (GSR) electrodes will be placed on the volar proximal phalanges of the fingers on the palms of the non-dominant hand. Participants will be instructed to maintain their visual attention to the computer monitor, avoid closing their eyes as much as possible, and will be told that the task is simply to immerse themselves into each video. Participants will be provided over-the-ear headphones, and the lights will be dimmed to further immerse participants into the videos. An investigator/research assistant will always remain seated quietly beside the participant but out of the participant’s direct view.

A continuous ECG and GSR recording for the entire procedure will start and a baseline assessment of the current self-reported emotions using the Positive and Negative Affect Schedule (PANAS) [70], will be collected.

After the baseline assessment has been completed, the transcutaneous electrical vagus nerve stimulation, delivered through a taVNS device (tVNS® R - tVNS technologies, Germany), will start. First, the taVNS device will be described and the taVNS electrode positioned at either the ear concha (active taVNS) or ear lobe (sham taVNS). The device consists of a stimulation unit and an ear electrode that is worn like an earphone. The stimulation unit sends electrical impulses through the electrode, which stimulates a branch of the vagus nerve transcutaneously (through the skin) in the auricle. The device can stimulate at an intensity between a minimum of 0.1 mA to a maximum of 5.0 mA with a biphasic waveform, an impulse duration of 28 s on and 32 s off, and an impulse frequency of 25 Hz. The stimulation intensity will be adjusted for every subject gradually by 0.1 mA at time until a tingling sensation or pulsation can be felt at the stimulation location. The stimulation should be clearly noticeable but not painful or uncomfortable. The device is CE-marked, indicating conformity with European Union regulations for medical devices, for the following conditions: anxiety, asthma, atrial fibrillation, autism, cognitive impairment, Crohn’s disease, depression, epilepsy, fibromyalgia, inflammation, migraines, Parkinson’s, Prader-Willi yndrome, sleep disorders, stroke, tinnitus. However, it is important to clarify that while the device has obtained CE marking, it has not received approval from the FDA or the EMA for the treatment of the listed conditions.

Four minutes after the optimal stimulation dose has been reached, the affect induction procedure will start. The affect induction procedure that will be used in this trial was developed by Daros and colleagues [71]. It has been shown to be tolerable and able to evoke higher negative emotional arousal in BPD patients in comparison with healthy controls [71]. It consists in the presentation on a computer screen of four (one neutral and three affect evoking) 4-min-long videos in sequence, each of which is followed by a 4-min post-induction period during which participants will rate the quality and intensity of the emotions perceived (PANAS) (post-induction ratings) and the perceived effectiveness in managing their emotions (PEME) [32].

The neutral video depicts a mother attempting to show a father that their young son can play chess and elicited very low levels of emotions in an undergraduate sample [72]. The three negative clips depicted a scene of domestic abuse between a man and a pregnant female partner; a funeral scene where a young girl struggles with the death of her friend; and a scene involving sexual assault by a police officer toward a woman while her husband watches. The domestic abuse clip significantly increased negative mood in a community-sourced sample [73]. The funeral clip elicited sadness in an undergraduate sample, whereas the sexual assault clip elicited anger, disgust, and contempt [72].

The titles and years of production of the films from which the videos are taken are *Searching for Bobby Fischer* (1993; neutral), *Nil by Mouth* (1997; domestic violence), *My Girl* (1991; funeral), and *Crash* (2004; sexual abuse).

After every post-induction period, for the three emotion-inducing videos, the participants will have other 90 seconds to rate again the PANAS (recovery ratings) (see Table 1). The neutral video will be always presented first to allow participants to orient themselves to the procedure. The three affect-evoking videos will be instead presented in a random order using the “randomizer” function of a Qualtrics software [74] (see below). Each page will be locked with a visible timer to ensure that all participants will progress through the procedure at the same pace. If a participant finishes the questions in advance, he/she will be instructed to sit quietly until the next page appears.

At the end of the survey, participants will answer additional questions on the quality of their participation (PQE).

All the instructions, questions, videos, and rating scales will be administered through an online Qualtrics survey [74], with time-fixed auto-advance according to the protocol-defined exposition time for every step of the experiment (see Table 1).

The software IMotions [75] will be used to integrate the data collected from the Qualtrics Survey and from the ECG and GSR sensors.

### Criteria for discontinuing or modifying allocated interventions {11b}

Each participant has the right to withdraw from the study at any time. In addition, the investigator may discontinue a participant from the study at any time if the investigator considers it necessary for any reason, including ineligibility (either arising during the study or retrospective having been overlooked at screening), significant protocol deviation, significant non-compliance with study requirements, an adverse event which requires discontinuation of the taVNS or results in inability to continue to comply with study procedures, emotional crisis which results in inability to continue to comply with study procedures or consent withdrawn.

The reason for withdrawal will be recorded in the electronic Case Report form (eCRF) (Qualtrics module) and in a research note in the patient research diary. If the participant is withdrawn due to an adverse event, the investigator will arrange for follow-up visits or telephone calls until the adverse event has resolved or stabilized.

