In animal studies, the stimulation of the vagus nerve through iVNS has been shown to produce an immediate dose-dependent anxiolytic effect [55] and to enhance fear extinction and reduce anxiety in rat models of PTSD, after both, moderate [56, 57] and prolonged and repeated trauma [58]. In humans, taVNS has been shown to reduce anger outbursts in adults with Prader-Willi Syndrome [59], enhance recognition of emotions in healthy students [60], and improve depressive and anxiety symptoms in adults and adolescents with clinically-diagnosed depression albeit with uncertain evidence due to the scarcity of available controlled studies [41]. Moreover, 4 weeks of taVNS has been shown to increase amygdala functional connectivity in patients with depression in comparison with sham taVNS [61]. A single session of taVNS has been shown to acutely alter the recognition of briefly presented facial expressions of negative valence in adolescents with MDD and increase emotion recognition in controls [62], as well as boost mood after prolonged effort exertion in healthy participants [63], in comparison with sham taVNS. In sum, taVNS has been shown to be safe and well-tolerated in humans at the doses tested, with local skin irritation being the most common side effect, followed by headache and nasopharyngitis [64].

To our knowledge, the effect of taVNS on emotional vulnerability in individuals diagnosed with BPD has never been investigated.

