## Assignment of interventions: blinding

### Who will be blinded {17a}

Only the trial participants will be blinded (single-blind). The two treatments taVNS and sham taVNS will be potentially indistinguishable for participants but not for investigators, since both groups will perceive the electrical stimulation even if at two different locations at the ear (concha for taVNS and ear lobe for sham taVNS). The eventual collection of information by the participant on the taVNS method and the correct positioning of the electrode to reach a stimulation of the vagus nerve could lead to a potential unblinding for the participants too.

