### Methods in analysis to handle protocol non-adherence and any statistical methods to handle missing data {20c}

In case of missing response to the PANAS at any post-induction stage, a mean value of other post-induction stage measurements will be used. Since the study is a single-session study under clinician oversight, we do not expect any missing variables.

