### Adverse event reporting and harms {22}

All AE’s occurring during the study observed by the investigator or reported by the participant, whether or not attributed to the device under investigation will be recorded on the eCRF as specified in the protocol. All Adverse device effects (ADE) will be recorded in the eCRF.

The following information will be recorded: description, date of onset and end date, severity, assessment of relatedness to device, other suspect drug or device, and action taken. Follow-up information should be provided as necessary.

The relationship of AEs to the device will be assessed by a medically qualified investigator or the sponsor/manufacturer and will be followed up until resolution or the event is considered stable.

All ADEs that result in a participant’s withdrawal from the study or are present at the end of the study, will be followed up until a satisfactory resolution occurs.

The Sahlgrenska University Hospital and the Department of Psychiatry for Affective Disorders will undertake an initial review of the information and ensure it is reported to the manufacturer. Events will be followed up until resolution, any appropriate further information will be sent by the research team in a timely manner.

Reporting to Läkemedelsverket will be done in liaison with the Chief Investigator and the Manufacturer.

In addition to the above reporting the Chief Investigator will submit once a year, throughout the trial, or on request a progress/safety report to Sahlgrenska University Hospital and Västra Götaland Region.

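### An adverse event that stops the stimulator may, on that ground alone, end study participation; later ratings a participant could still give may be lost or filled from the neutral clip

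*Protocol article*

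**What the plan says.** The protocol article, section Criteria for discontinuing or modifying allocated interventions {11b}, says that "the investigator may discontinue a participant from the study at any time if the investigator considers it necessary for any reason". It then lists grounds. One is "an adverse event which requires discontinuation of the taVNS or results in inability to continue to comply with study procedures"; another is "emotional crisis which results in inability to continue to comply with study procedures".

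For what happens afterwards, {11b} requires the reason for withdrawal to be recorded and an adverse event to be followed up. Section {18b} on retention asks a participant who discontinues for any reason to complete the participation-quality questions (PQE), and offers a follow-up visit if the cause was an adverse event. The harms section {22} also foresees adverse device effects that lead to withdrawal from the study and promises follow-up of them. None of these places mentions the remaining PANAS or PEME ratings.

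On missing data, section {20c} says: "In case of missing response to the PANAS at any post-induction stage, a mean value of other post-induction stage measurements will be used". It adds that no missing variables are expected. Section {11a} fixes the neutral clip as the first of the four.

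**The concern.** The adverse-event ground has two limbs joined by 'or'. The first, that the stimulation has to stop, is enough even when the participant can still comply. The emotional-crisis ground in the same sentence applies only with inability to comply. The text therefore ties leaving the study to stopping the device, which are separate events in a session where the outcomes are on-screen self-ratings.

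The background section reports taVNS as well tolerated, "with local skin irritation being the most common side effect". Irritation could call for removing the ear electrode without preventing anyone from watching a clip and rating it. If she is then discontinued, ratings are lost for a treatment-related reason although they were obtainable. The person deciding knows the arm, because only participants are blinded ({17a}).

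The missing-data rule adds a second problem. It does not say whether it covers participants who stop early. If it does, the scores filled in for distressing clips come wholly or partly from a clip chosen because it evokes little emotion.

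**Working it through.** **Inputs.** Post-induction PANAS at t3 (neutral), t4, t6 and t8; recovery PANAS at t5, t7 and t9; PEME at t3, t4, t6 and t8 (sections {12} and {18a}). Planned size 42, 21 per arm, from 34 evaluable ({14}).

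**The plan's own figure.** 34 × 1.25 = 42.5; the article states 42. The attrition allowance is 42 − 34 = 8 participants from all causes. The article does not say how many of these would be stops of stimulation.

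**Ratings lost if she leaves just after a given rating, and the neutral clip's share of a filled score.** I read {20c} as averaging the participant's own other post-induction values. The neutral share is then 1/(number of post-induction ratings already given).

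| Leaves just after | Post-induction PANAS lost | Recovery PANAS lost | PEME lost | Neutral share of each filled score |
|---|---|---|---|---|
| t3 | 3 of 4 (t4, t6, t8) | 3 of 3 | 3 of 4 | 1/1 = 100% |
| t4 | 2 of 4 (t6, t8) | 3 of 3 | 2 of 4 | 1/2 = 50% |
| t6 | 1 of 4 (t8) | 2 of 3 (t7, t9) | 1 of 4 | 1/3 = 33% |

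A stop before t3 loses all four post-induction ratings and leaves the rule nothing to average. The rule names only post-induction PANAS, so lost recovery and PEME ratings are not filled in any case. If the mixed model of {20a} uses her available ratings unfilled, the substitution in the last column does not occur.

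**Cost of collecting ratings with the device off.** Take the mean effect over the three negative clips, and assume no effect once the device is off. One taVNS participant with k of three clips unstimulated, among n analysed in that arm, dilutes the effect by (k/3)/n.

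| Device stops | n = 21 | n = 17 (34 evaluable, split equally) |
|---|---|---|
| before the first negative clip (k = 3) | (3/3)/21 = 4.8% | (3/3)/17 = 5.9% |
| just after t4 (k = 2) | (2/3)/21 = 3.2% | (2/3)/17 = 3.9% |
| just after t6 (k = 1) | (1/3)/21 = 1.6% | (1/3)/17 = 2.0% |

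No bias in PANAS units or SDs is computed: the article gives neither the neutral-to-negative rise nor a rate of stops by arm.

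**The case against.** The strongest reply is that nothing here is stated wrongly. The verb is 'may', further ratings are not forbidden, and the same sentence allows discontinuation for any reason, so deleting the adverse-event ground would leave the investigator's power unchanged. Provision for ratings after a stop could stand in the full protocol, which is not shown. There is also a case for the rule: the remaining clips show domestic abuse, a funeral and a sexual assault, and ratings with the device off do not measure response under stimulation. Finally, intensity is titrated so that "The stimulation should be clearly noticeable but not painful or uncomfortable", so few stops are likely.

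Much of this stands. It limits the point to a minor one and is why safety discretion should stay. It does not remove the point, because the article goes beyond silence: it names stopping the device as a ground for leaving the study, names the PQE as what is then collected, and gives a fill rule with no exception for early stoppers.

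It can also be said that the fill rule is weak whatever {11b} says. That is true, but the discontinuation rule is one route by which a participant would reach it.

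A reader might infer that the plan requires withdrawal whenever stimulation stops, or that an unblinded investigator will cause unequal loss between arms. The documents support neither. The wording only permits withdrawal, and no rate of stops or difference between arms is given, so unequal loss is a possibility only.

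**Conclusion.** The point holds as a minor one. Section {11b} allows participation to end solely because the device had to stop, and with {18b} this can lose PANAS and PEME ratings that were still obtainable. Applied literally, {20c} would then replace missing negative-clip scores with values resting 100%, 50% or 33% on the neutral clip. These shares assume a stop just after t3, t4 or t6, and a rule that covers early stoppers and averages the participant's own ratings.

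The frequency of such stops and the direction of any bias are unknown. The effect is probably small, given titration to comfort, the reported tolerability, and a mixed model that can use ratings given before the stop. The 8-participant allowance is not an estimate of losses by this route.

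**What to change.** In {11b}, state that stopping stimulation does not by itself end participation. The scheduled clips and the PANAS and PEME ratings continue if the participant is willing and able and the investigator sees no safety concern; she is analysed as randomised; and the time point of the stop is recorded. The investigator's discretion to stop for safety stays as it is.

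In {20c}, state that the mean fill is not used for participants who stop early for any reason, and that the mixed model of {20a} uses their available ratings.

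The cost is two or three sentences in {11b}, one in {20c}, and one eCRF field beside the reason for withdrawal already recorded. The statistical price is the dilution shown in the working. Device-off ratings may also partly reflect the adverse event itself, which an as-randomised comparison counts.

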### Strategies to improve adherence to interventions {11c}

The investigator will sit in the experiment room together with the participant monitoring all the phases of the experiment and be available to help with any eventual problems or difficulties that may emerge in complying with the study procedure. All the instructions and the outcome scales will be administered on a computer screen using a Qualtrics survey with fixed time, enough to read the instructions and answer all the questions, and auto-advance (participants will not be able to advance to the next question by themselves). The participant will sit comfortably in front of a computer screen wearing a headset to reduce the influence of potentially distracting environmental noise and facilitate the immersion in the task. A continuous ECG will be recorded throughout the experiment and an HRV analysis will be performed to check if taVNS was able to activate the vagus nerve in the active group. The galvanic skin response (GSR) will be also measured throughout the entire procedure to control that the affect-inducing procedure was able to generate emotional arousal independently of the participants’ self-scores for emotional arousal. After the experiment completion, participants will be asked to evaluate the quality of their participation with questions on the perceived empathy with the video characters, eventual avoidance behaviors during the affect evoking procedure, the impact of the presence of the investigator in the room on their ability to attend the procedure, the level of attention during the task, the presence of eventual distractors or other barriers, suggestions to reduce the eventual burden of participation.

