## Assignment of interventions: allocation

### Sequence generation {16a}

The computerized random number generator is used to generate random sequences on a 1:1 basis. The random sequence will be put into a sealed, opaque, and sequentially numbered envelope by a team member not involved in the enrolment and investigation procedures. When the participant is admitted to the operating room the investigator will sequentially open the envelopes, based on their numbered order, to obtain a random sequence to determine the grouping. Participants with random sequences 1–21 are assigned to group taVNS, while 22–42 are assigned to group sham taVNS. Each participant will be given a unique study sequential number on the envelope cover in the order of their participation in this study. The random sequences of all participants and their corresponding study sequential numbers will be recorded.

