### Plans to promote participant retention and complete follow-up {18b}

The study was designed to minimize as much as possible the burden for the participants. The entire procedure will be completed in a period of two hours during which the investigator will always be present in the room to assist the participant with all potential problems or difficulties experienced. In case of discontinuation of participation for any reason, the participant will be asked to complete the PQE (see above) to further assess the reasons for discontinuation if not directly expressed by the participant or evident to the investigator. A follow-up visit will be offered to the participant in case of discontinuation due to AE.

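### Staff who are not blinded to the arm sit in on every film and self-rating, and the article is inconsistent on who sits in and how far help may go: an uncontrolled risk of performance bias

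*Protocol article*

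**What the plan says.** All points are from the protocol article.

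- **Blinding {17a}:** "Only the trial participants will be blinded (single-blind"). The same section says that investigators can tell the two treatments apart.
- **Allocation {16a}:** when the participant is admitted, "the investigator will sequentially open the envelopes, based on their numbered order". The investigator therefore knows the arm before the session starts.
- **Who sits in, {11a}:** "An investigator/research assistant will always remain seated quietly beside the participant but out of the participant’s direct view".
- **Help, {11c}:** the investigator is in the room during all phases and is to "be available to help with any eventual problems or difficulties that may emerge in complying with the study procedure".
- **Help, {18b}:** "the investigator will always be present in the room to assist the participant with all potential problems or difficulties experienced".
- **Stopping, {11b}:** "the investigator may discontinue a participant from the study at any time if the investigator considers it necessary for any reason". The listed reasons include "emotional crisis which results in inability to continue to comply with study procedures". The reason for a withdrawal is recorded in the eCRF.
- **Outcomes {12}:** the primary outcome is self-rated negative affect (PANAS-N), and one secondary outcome is self-rated difficulty in managing emotions (PEME).

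**The concern.** The sham controls for the sensation of stimulation. It does not control for what a person who knows the arm says or does while the participant watches a distressing film and then rates her distress. A word of reassurance, encouragement to carry on or a decision to stop can each move PANAS-N or PEME. If any of these happened more often in one arm, the difference would appear in the primary comparison as an effect of taVNS. The sitter's manner could also give away the arm.

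The single-blind limit is acknowledged in {17a}, but the only route to participant unblinding named there is the participant's own reading about electrode placement. The sitter is not discussed.

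**Working it through.** **Step 1. The sections side by side.**

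| Section | Who is present | What that person may do |
|---|---|---|
| Intervention description {11a} | investigator or research assistant | sit quietly, out of direct view |
| Adherence {11c} | investigator | help with difficulties in following the procedure |
| Retention {18b} | investigator | assist with all problems or difficulties experienced |

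Sitting quietly by default and helping when a procedural problem arises are compatible, so {11a} and {11c} do not clash on help alone. Two differences remain.

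- Role: {11a} allows an assistant, whereas {11c} and {18b} name only the investigator.
- Scope: {11c} covers procedural difficulty. The wording of {18b} has no such limit and could include emotional support during a film.

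**Step 2. Does the sitter know the arm?** An investigator does, having opened the envelope {16a}. A research assistant need not, but {17a} plans no blinding for any staff.

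**Step 3. Size.** The document gives no figure for this, so there is no stated number to reproduce. What follows is an illustration on assumed inputs.

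- From the Sample size section {14}: 21 per arm and alpha 0.05.
- Assumed: a true null, and a spurious shift b (in SD of the rating) in the difference between arms.
- Formula: two-sided t test with df = 2 × 21 − 2 = 40 and critical value 2.021. The noncentrality is b × √(21/2).

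| Assumed shift b | Noncentrality | Chance of rejecting a true null |
|---|---|---|
| 0.05 SD | 0.162 | 5.3% |
| 0.1 SD | 0.324 | 6.2% |
| 0.2 SD | 0.648 | 9.7% |

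What could produce such shifts? If k of 21 participants in one arm only are helped, and each rating falls by δ SD, then b = (k/21) × δ.

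- k = 2, δ = 0.5: 2/21 × 0.5 = 0.048 SD.
- k = 4, δ = 1: 4/21 × 1 = 0.19 SD.

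Both k and δ are assumptions. The upper case also supposes help at every film. Section {14} counts four post-induction ratings, so help confined to one film would move their average by about a quarter as much: 0.19/4 = 0.048 SD.

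**The case against.** The case against is substantial.

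1. **Imbalance.** A reader might infer an unbalanced co-intervention. The document does not support that: presence is the same in both arms, and nothing says that help differs. This stands, and the point is therefore put as a risk.
2. **Avoidability.** A reader might also infer that the sitter is the person who placed the electrode, and that the over-the-ear headphones would hide the site from anyone entering later. Neither is stated. Placement is described in the passive, and nothing is said about what the headphones cover. This stands.
3. **Existing safeguards.** The survey pages are locked, timed and auto-advancing. Participants wear headphones in dimmed light, with the sitter out of view. GSR gives a measure outside self-report, and the end-of-session questions ask whether someone's presence made it hard to experience the emotions. These reduce the risk. They do not record what help was given, and reassurance could move GSR too.
4. **Left to the full protocol.** Session scripts and contact logs commonly sit there, and it is not shown. Their absence from the article is no finding. The finding is that the article's own statements differ in role and scope.
5. **Supervision.** Replacing the investigator in the room would change supervision of patients watching assault scenes and may need a second staff member. This stands, so such a replacement is not made a requirement.

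**Conclusion.** The point holds as an uncontrolled risk of performance bias on self-rated PANAS-N and PEME, together with an inconsistency between {11a}, {11c} and {18b} that needs reconciling. It does not hold as evidence that the arms are or will be treated differently.

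The size cannot be derived from the document. The range of about 5% to 10% for the error rate rests wholly on assumed shifts of 0.05 to 0.2 SD with 21 per arm, and the top of that range needs help concentrated in one arm and at every film.

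A reader might further infer that stopping the most distressed participants in one arm would remove them, and so lower that arm's mean. This assumes that their earlier ratings are discarded, which the article nowhere says. Its statistical sections {20a} and {20c} describe a mixed model and the filling of missing post-induction ratings from other stages. Whether that filling is sound is a separate question. The change below is worth making because it is cheap and closes a real route of bias.

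**What to change.** - Reconcile {11a}, {11c} and {18b} so that they name the same role and the same scope of help.
- Between t2 and t9, limit contact that is not safety-related to one fixed script, identical in both arms.
- Log any other contact, and any stop, by stage in the eCRF, and report both by arm.
- Where a research assistant is already present under {11a}, prefer as sitter one who was absent at allocation and electrode placement. Do not assume that the headphones conceal the site.
- Safety-related help and stopping decisions stay as the sponsor has them.

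**Cost:** a short script, one eCRF field and a wording change in three sections. Trial status gives March 2023 as the start of recruitment, so sessions already held cannot be brought under the script. The date of the change should be reported. The assistant preference adds no staff where one is already there.
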